**Methods:**

First, a randomized, double-blind, placebo-controlled intervention study will be conducted on 340 pregnant females with babies at high risk for AD. These subjects will be randomly divided into four groups of different doses of *L. reuteri* FN041 (1 × 10^9^, 5 × 10^9^, and 1 × 10^10^ CFU/d) along with a placebo. The safety and efficacy of maternal use of *L. reuteri* FN041 for preventing infantile AD will be analyzed, and the most efficient dosage of *L. reuteri* FN041 will be determined. Subsequently, a multicenter cohort study of 500 pregnant females with babies at high risk for AD will be conducted to promote the maternal application of *L. reuteri* FN041. These subjects will be administered *L. reuteri* FN041 at the optimal dose determined during the first stage of late pregnancy and lactation, and their babies will be analyzed for AD development. Recruitment was initiated in October 2022.

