### Trial design

The study is divided into two stages. In the first stage, a multicenter, randomized, double-blind, placebo-controlled intervention study will be conducted in 340 pregnant females with babies at high risk for AD recruited from the Wuxi Maternity and Child Health Care Hospital affiliated with Jiangnan University and the Affiliated Hospital of Qingdao University. These subjects will be randomly divided into four groups (*n* = 85 for each group): (1) placebo group administered with the carrier solid beverage daily, (2) group administered with *L. reuteri* FN041 solid beverage at a dose of 1 × 10^9^ CFU/d, (3) group administered with *L. reuteri* FN041 solid beverage at a dose of 5 × 10^9^ CFU/d, and (4) group administered with *L. reuteri* FN041 solid beverage at a dose of 1 × 10^10^ CFU/d. Their offspring will be examined for AD development during the 2 years after birth so that the efficacy of maternal use of *L. reuteri* FN041 in the prevention of AD can be analyzed by calculating the cumulative incidence of AD in infants. Adverse reactions will be also recorded. Studies have reported that the most efficient dosage of *L. reuteri* FN041 can be determined within 6 months after birth, as infantile AD often develops in early life and peaks in the third month of life (Guo et al., 2019).

In the second stage of *L. reuteri* FN041 promotion and application, a multicenter cohort study in an expanded research population will be conducted. A total of 500 pregnant females with babies at a high risk for AD will be recruited from four tertiary hospitals: Wuxi Maternity and Child Health Care Hospital affiliated with Jiangnan University, Affiliated Hospital of Qingdao University, Suzhou Municipal Hospital, and Changzhou Maternal and Child Health Hospital. These subjects will be administered with *L. reuteri* FN041 at the optimal dosage determined in the first stage during late pregnancy and lactation; subsequently, their babies will be followed up for AD development for 2 years after birth.

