### Participant timeline

Pregnant females will be recruited at 14–16 weeks of gestation and receive intervention strategy at 32–36 weeks of gestation. Their infants will be followed-up for 2 years after birth. Clinical follow-up will be conducted in the hospital at 1, 3, 6, 8, and 12 months of age, and telephone follow-up will be conducted at 2, 4, 5, 10, and 24 months of age. Two specific pediatric attending doctors are responsible for the clinical follow-up of the infants. Infants suspected of having AD will be referred to the pediatric dermatology clinic, and two designated pediatric dermatologists will jointly diagnose and assess disease severity. Questionnaire surveys will be completed at each clinical and telephone follow-up. Parents will be instructed to contact the project team immediately and take the infant to two designated pediatric dermatologists for diagnosis and treatment if the baby is suspected of developing AD during 0–2 years of age. A detailed flowchart of the study is shown in Figure 1.

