### Data collection and sample collection

Clinical follow-up of the infants will be conducted at 7 and 42 days of age, and telephone follow-up will be conducted at 6, 12, and 24 months of age. Questionnaire surveys will be completed at each clinical and telephone follow-up. The infant-specific questionnaire is designed based on the International Study on Asthma and Allergy in Children. Detailed information on birth parity, number of births (single or multiple births), gestational age, mode of delivery, weight (including birth weight), length (including birth length), feeding mode (breast, formula-, or mixed-fed), maternal and infant exposure to antibiotics and probiotics, parental smoking, family history of allergic diseases, infection, and other potential confounding factors will be recorded.

The mother’s feces will be collected within 1 week before intervention with solid beverage and the first week after delivery, whereas breast milk samples (approximately 5–10 mL each time) will be collected at 1–6 (colostrum), 7–15 (transitional milk), and 16–30 (mature milk) d after childbirth. Cord blood will be collected at the time of birth. Fecal samples (approximately 0.5–6 g each time) will be collected from infants in the colostrum, during transitional lactation, and at the ages of 1, 6, and 12 months after birth.

The maternal dietary survey is designed to be carried out before and after probiotic intervention (that is, 6 months after delivery). The dietary and nutritional status survey will be conducted using a 24-h dietary recall method to investigate the intake of various foods by the study participants within 3 days. Their energy and nutrient intake will be analyzed. The food frequency questionnaire will be used to collect information on the types and frequencies of food intake among all study participants and evaluate their dietary structure.

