### Outcomes

#### Primary outcomes

In both stages of the trial, the cumulative incidence of AD within 2 years of delivery will be analyzed as the primary outcome. The diagnosis of AD is based on the Williams standard, as previously described, which is widely applicable to outpatient and general population epidemiological investigations in research (Williams et al., 1994). Skin itching is the primary criterion. The secondary criteria are as follows: (1) history of skin involvement on the flexor side, including the cubital fossa, cochineal fossa, anterior malleolus, and neck; (2) history of asthma, allergic rhinitis, or AD in first-degree relatives of children under 4 years of age; (3) history of dry skin throughout the body; (4) eczema on the flexed side (on the cheek or forehead and limbs on the extended side in children under 4 years of age); and (5) onset before the age of 2 years. Infants who meet the main criteria, along with three or more secondary criteria, will be diagnosed with AD. Once diagnosed with AD, disease severity will be assessed using the SCORAD index. Accordingly, infants will be divided into mild (SCORAD: 0–24 points), moderate (SCORAD: 25–50 points), and severe (SCORAD: >50 points) groups (Oranje et al., 2007).

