### Trial status

This study is in its first stage, from October 2022 to December 2025. Subject recruitment in the first stage commenced from July 2023 and will be continued till December 2023. Subject recruitment in the second stage will start from July 2024 to December 2024.

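### The stated end of Stage 1, December 2025, falls about five to six months before the last infants reach the 24-month primary outcome

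*Protocol article*

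**What the plan says.** Trial status gives the period of Stage 1: "This study is in its first stage, from October 2022 to December 2025". The same section gives its recruitment window: "Subject recruitment in the first stage commenced from July 2023 and will be continued till December 2023". The Methods part of the abstract gives another start: "Recruitment was initiated in October 2022".

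Under Primary outcomes, for both stages, "the cumulative incidence of AD within 2 years of delivery will be analyzed as the primary outcome". Trial design and Participant timeline also commit to two years of infant follow-up. Participant timeline sets recruitment at 14–16 weeks of gestation.

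The article has two contact schedules. Participant timeline has hospital visits up to 12 months, and "telephone follow-up will be conducted at 2, 4, 5, 10, and 24 months of age". Data collection and sample collection has clinical visits at 7 and 42 days, and "telephone follow-up will be conducted at 6, 12, and 24 months of age". The two differ, but neither has a planned contact between 12 and 24 months. Participant timeline also tells parents to contact the team at once if they suspect AD at any time in the first two years.

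**The concern.** A woman recruited early in the second trimester delivers about half a year later, and her infant needs two more years to reach the primary time point. Recruitment to the end of 2023 therefore implies follow-up to about the middle of 2026. A Stage 1 that ends in December 2025 does not contain that follow-up.

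At stake is how completely the primary outcome is ascertained in the randomised comparison. The 24-month telephone call is the only planned contact after 12 months. An infant who had not reached it by closure would have been seen or called on schedule for the last time at 12 months. Any later case would be known only if a parent had reported it.

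**Working it through.** **Inputs**
- Stage 1 recruitment: July to December 2023 (Trial status), or from October 2022 (abstract). Months are read as first to last day unless noted.
- Gestation at recruitment: 14–16 weeks (Participant timeline).
- Primary time point: 24 months after delivery (Primary outcomes).
- Stated end of Stage 1: taken as 31 December 2025 (Trial status).
- Assumptions not in the article: birth at 37–40 weeks, and recruitment spread evenly over the window.

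**When the last infant reaches 24 months**

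Birth date = recruitment date + (weeks at birth − weeks at recruitment). For a woman recruited on 31 December 2023:

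| Birth at | Recruited at | Weeks added | Birth | 24 months |
|---|---|---|---|---|
| 40 weeks | 14 weeks | 26 | 30 Jun 2024 | 30 Jun 2026 |
| 40 weeks | 16 weeks | 24 | 16 Jun 2024 | 16 Jun 2026 |
| 37 weeks | 14 weeks | 23 | 9 Jun 2024 | 9 Jun 2026 |
| 37 weeks | 16 weeks | 21 | 26 May 2024 | 26 May 2026 |

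So the stated December 2025 is not reproduced. The last infants reach 24 months about five to six months later. If recruitment stopped on 1 December 2023, these dates would move 30 days earlier, to about late April to the end of May 2026, still after the stated end.

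**Share at 24 months on 31 December 2025**

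An infant qualifies only if born by 31 December 2023. Subtracting 26, 24, 23 or 21 weeks gives a latest qualifying recruitment date of 2 July, 16 July, 23 July or 6 August 2023.

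*July 2023 start.* The window of 1 July to 31 December has 184 days, and the qualifying days are 2, 16, 23 and 37:
- birth at 40 weeks: 2/184 = 1.1% to 16/184 = 8.7%
- birth at 37 weeks: 23/184 = 12.5% to 37/184 = 20.1%

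Under 24 months: 100 − 20.1 = 79.9% to 100 − 1.1 = 98.9%, or about 272 to 336 of 340 infants.

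*October 2022 start.* The window has 457 days from 1 October 2022, or 427 days from 31 October:
- most favourable (1 October, birth at 37 weeks, recruited at 16 weeks): 310/457 = 67.8%
- least favourable (31 October, birth at 40 weeks, recruited at 14 weeks): 245/427 = 57.4%

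Under 24 months: 32.2% to 42.6%, or about 109 to 145 of 340.

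Stopping recruitment on 1 December 2023 would raise the largest shares at 24 months to 37/154 = 24% (July start) and 310/427 = 73% (1 October start). The conclusion is the same.

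**Ages at the stated end**

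The youngest infants, born between 26 May and 30 June 2024, would be about 18 to 19 months old. All would have passed the 12-month contact by 30 June 2025.

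**Likely number of late cases**

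Sample size calculation quotes cumulative incidences in high-risk infants of 40.1% at one year and 41% at two. The difference is 0.9 percentage points, and 0.009 × 340 ≈ 3 infants. This is only indicative, because the two figures come with citations to different studies and describe infants outside this trial.

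**The case against.** The strongest reply is that December 2025 appears once, in a status note, while every operative section commits to two years. Nothing in the article says that follow-up stops or that infants are censored on that date. If it is a slip, the two-year commitment governs and no data are lost. That is fair, and it limits the consequence to a conditional one. The date is still wrong against the design and should not stand.

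The second reply is that little would be lost even if the date were followed. Every infant would be at least about 18 months old and past the 12-month contact, parents are told to report suspected AD at any time, Trial design places the peak in the third month, and the planning incidences barely rise between one and two years. This also stands. A reader might infer that the primary outcome would be lost for most infants; the documents do not support that. What would be lost is the closing contact, and the size of that group depends on which recruitment start is right.

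Reading December 2025 as the end of the whole study does not help. Of Stage 2 the article says "Subject recruitment in the second stage will start from July 2024 to December 2024". A woman recruited on 1 July 2024 at 16 weeks who delivers at 37 weeks gives birth on 25 November 2024, so no such infant reaches 24 months before late November 2026.

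A reader might also infer from the same dates that Stage 2 must begin before the dose can be chosen. The first Stage 2 dose could fall on 21 October 2024 (1 July plus 16 weeks, from week 16 to week 32), while the last Stage 1 infants reach six months on 16–30 December 2024 if born at 40 weeks. The documents do not support calling this an error. Trial design says that the dose "can be determined within 6 months after birth" and points to the month-3 peak. A three-month readout would be complete by 16–30 September 2024, and earlier births or other readings of the stated months can close the six-month gap. Which readout decides is a detail that an article may leave to the full protocol.

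**Conclusion.** The point holds for the Stage 1 end date. On the article's own recruitment window and gestational ages, the last infants reach the primary time point in about late May to June 2026, and neither stated recruitment start changes that. The share of infants short of 24 months is about 80–99% with the July 2023 start and about 32–43% with the October 2022 start. Both ranges assume even recruitment, birth at 37–40 weeks and recruitment to 31 December 2023.

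The contradiction in dates is certain; its consequence is conditional. It bites only if Stage 1 is closed or analysed as dated, and then the number of missed cases is probably small. The conflicting recruitment starts are a separate inconsistency. Trial status itself dates the stage from October 2022 and recruitment from July 2023, so the abstract may have given the start of the stage as the start of recruitment, but the article does not say so.

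**What to change.** - Change the stated end of Stage 1 in Trial status to at least July 2026.
- State that the primary analysis of Stage 1 is run only after every infant's 24-month contact is due and has been attempted.
- Reconcile October 2022 and July 2023 as the start of Stage 1 recruitment, in the abstract and in Trial status.

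These are changes of date and wording. The cost is that Stage 1 closes about seven months later (December 2025 to July 2026), with the staff time to keep the telephone follow-up running until then. No change to the sample size, the intervention or the visits is needed.

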## Data availability statement

The original contributions presented in the study are included in the article/supplementary material, further inquiries can be directed to the corresponding authors.

## Abbreviations

AD: Atopic dermatitis
*L. reuteri*: *Limosilactobacillus reuteri*
RCT: randomized controlled trial
HN001: *Lactobacillus rhamnosus* HN001
LGG: *Lactobacillus rhamnosus* GG
sIgA: secretory immunoglobulin A
IFN-γ: interferon-γ
Tregs: regulatory T cells
IL: interleukin
